## Abstract

**Background:**

Clinically effective and cost-effective methods for managing problematic sexual behaviour in adolescents are urgently needed. Adolescents who show problematic sexual behaviour have a range of negative psychosocial outcomes, and they and their parents can experience stigma, hostility and rejection from their community. Multisystemic therapy (MST) shows some evidence for helping to reduce adolescent sexual reoffending and is one of the few promising interventions available to young people who show problematic sexual behaviour. This paper describes the protocol for Services for Teens Engaging in Problem Sexual Behaviour (STEPS-B), a feasibility trial of MST for problem sexual behaviour (MST-PSB) in antisocial adolescents at high risk of out-of-home placement due to problematic sexual behaviour.

**Methods/Design:**

Eighty participants and their families recruited from five London boroughs will be randomized to MST-PSB or management as usual with follow-up to 20 months post-randomization. The primary outcome is out-of-home placement at 20 months. Secondary outcomes include sexual and non-sexual offending rates and antisocial behaviours, participant well-being, educational outcomes and total service and criminal justice sector costs. Feasibility outcomes include mapping the clinical service pathways needed to recruit adolescents displaying problematic sexual behaviour, acceptability of a randomized controlled trial to the key systems involved in managing these adolescents, and acceptability of the research protocol to young people and their families. Data will be gathered from police computer records, the National Pupil Database and interviews and self-report measures administered to adolescents and parents and will be analysed on an intention-to-treat basis.

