### Sample size and power calculation

It is estimated that the Brandon Centre will have approximately two eligible cases per month, where referrals are obtained from a minimum of four boroughs, which would result in 72 cases randomized into the trial over the 3-year recruitment period. Five more boroughs are set to join the trial, resulting in nine boroughs in total; it is predicted that this will result in 34 eligible referrals per year, to give a total of approximately 102 cases randomized over 3 years.

Effect size has been estimated on the basis of the available data from a recent MST intervention study of sexual offenders in the United States [46]. As only summary statistics were available, 95 % confidence intervals for effect size were used and the lower limit chosen in a conservative approach. On the basis of the number of participants in the two groups who moved from offender to non-offender status during the follow-up period, the highly significant effect of treatment (*P* < 0.001, Fisher’s exact test) is 0.32 to 0.49 (Cramer, a medium to large effect). In the current study, non-offender status is defined as no arrest leading to conviction over the follow-up period, based on police computer records. We expect to achieve the lower end of the effect size range, given that the trial is mounted independently (although under the supervision) of the development team and involves the transportation of the clinical methodology across national boundaries, healthcare systems and cultures. A sample size estimate to give 80 % power based on the lower estimated effect size of 0.32 suggests 56 participants in a two-group design. Figure 1 shows the expected flow of participants from recruitment through to the end of the study.

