#### Primary outcomes

The primary outcome is the proportion of documented cases of offending within 20 months of randomization, based on police records supplemented by information obtained from the young person, parents/caregivers and social care services. While this may be only a partial or even an inaccurate reflection of the psychological conditions and social behaviours of the participants, it is the indicator of primary concern for the funders of the programme as, in most cases, this record triggers costly juvenile justice and social interventions. A linked outcome, of similarly high concern to funders of services, is assignment to long-term (3 months or longer) out-of-home placements in specialist residential provision when social services consider that the safety of the participant’s family or community is compromised by the individual, even in the absence of arrest and conviction. This means all participants who are placed into local authority care, are incarcerated, long-term hospitalized or offered residential schooling at any time in the 20 months following randomization will not be considered to have moved from the offending to the non-offending group. This information will be obtained from caregivers and cross-referenced with documented information from the national social care services database to maximize accuracy. The investigators expect this trial to give information on how many young people assigned to MAU and to MST-PSB require specialist residential provision either immediately after intervention or during the follow-up period.

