### Primary outcome

The primary outcome of the proportion of cases where a sexual offence has been incurred during the follow-up period will be described by a Kaplan-Meier graph and summarized by the proportions in each group with a new sexual offence by 20 months. The linked outcome of out-of-home placement will also be described by a Kaplan-Meier graph and summarized by the proportions in each group with out-of-home placement by 20 months. The number of events will be estimated in order to inform power calculations for a fully powered efficacy trial.

For time-to-event offending outcomes, the event rate will be estimated. For continuous secondary outcomes, such as questionnaire data, linear mixed effects models will be fitted in order to estimate the individual-level residual variance.

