The research is being conducted by a team based at UCL, with data collection from cases referred to the Brandon Centre. MST-PSB aims to reduce levels of both sexual and non-sexual offending in the target population, and so offending will be used as a key measure to determine whether the intervention is effective. In addition, as out-of-home placement (whether this constitutes incarceration, hospitalization, residential schooling or local authority care) represents an unhelpful outcome for antisocial adolescents in the majority of cases, the investigators have chosen to use preservation of the family (that is, the *absence* of out-of-home placement) as the main measure of potential benefit. Other possible benefits of MST-PSB will also be examined, such as the impact on the young person’s mental health and well-being, and that of the carer(s).

To address factors associated with improvement, the investigators have taken considerable effort to monitor the effect of MST-PSB on parenting and family functioning. It is anticipated that improvement observed in association with MST-PSB will be commensurate with the impact that the intervention has on variables within the family, and for other clinically critical outcomes (for example, antisocial peer group affiliation), to be in line with changes in the purported mediating processes [46].

To assess what the benefits of MST-PSB and MAU might be, care will be taken to gather accurate descriptions of the interventions delivered to both groups in the study. In addition, the investigators will attempt to chart the subjective experience of all stakeholders in the project (that is, participants, their carers and providers and commissioners of services). The data from the trial will be analysed to determine whether the expected benefit of MST-PSB is achieved and will provide initial data on whether MST-PSB represents an economically viable option for intervening with young people displaying problem sexual behaviour.

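### The article names three incompatible primary outcomes, so the headline comparison and the event rate for a full trial depend on which one is used

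*Protocol article*

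**What the plan says.** Three places in the protocol article name the primary outcome, and each names a different event.

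- **Abstract, Methods/Design:** "The primary outcome is out-of-home placement at 20 months". Offending is ranked below it: "Secondary outcomes include sexual and non-sexual offending rates and antisocial behaviours".
- **Assessments and outcome measures, Primary outcomes:** "The primary outcome is the proportion of documented cases of offending within 20 months of randomization, based on police records", supplemented by the young person, parents or caregivers, and social care services. Placement moves down a rank: "A linked outcome, of similarly high concern to funders of services, is assignment to long-term (3 months or longer) out-of-home placements". The same paragraph then says that a participant placed in care, custody, long-term hospital or residential school during the 20 months is not counted as having become a non-offender.
- **Statistical analysis plan, Primary outcome:** "The primary outcome of the proportion of cases where a sexual offence has been incurred during the follow-up period". Placement is again the linked outcome, with its own Kaplan-Meier graph and proportions.

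Two further sections bear on the choice. In Sample size and power calculation, "non-offender status is defined as no arrest leading to conviction over the follow-up period, based on police computer records". The Discussion calls offending a key measure but takes the absence of out-of-home placement "as the main measure of potential benefit". No section ranks or reconciles these statements.

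**The concern.** The Abstract and the Primary outcomes section exchange the ranks of placement and offending. The two methods sections that agree on offending then disagree on which offences count and on whether placement is folded in.

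Two things depend on the answer. The first is the headline comparison. The article describes the trial as a feasibility study, but it also says that the trial will evaluate effectiveness and show whether the expected benefit is achieved. A reader of the results cannot tell from this document which comparison was meant to carry that weight. The second is the number of events, which the Statistical analysis plan section intends to use for the power calculation of a full trial. A rate for sexual offences, one for all offences and one for placements would lead to different full trials.

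The source also matters. Under Screen 3 and consent, families are told their allocation. Offending supplemented by family report is therefore open to a reporting bias that the records-only definition in the sample size section avoids.

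**Working it through.** **1. The plan's own figure.** The sample size section gives 56 participants for 80% power at an effect size of 0.32. Alpha and sidedness are not stated; 5% is assumed here.

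- Chi-square with 1 df, N = (z_alpha + z_power)² / 0.32². Two-sided: (1.960 + 0.842)² / 0.1024 = 76.6, so 77. One-sided: (1.645 + 0.842)² / 0.1024 = 60.4, so 61.
- Reading 0.32 as a point-biserial correlation, d = 2 × 0.32 / √(1 − 0.32²) = 0.676, and n per arm = 2 × (z_alpha + z_power)² / d². One-sided this gives 28 per arm, 56 in total; two-sided it gives 70.

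Of the methods tried, only the one-sided point-biserial calculation reproduces 56. By the two-sided chi-square, the planned 80 has 82% power at 0.32. How 56 was derived is a separate question. What matters here is that it is tied to conviction status, which none of the three named primary outcomes matches as stated.

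**2. The definitions applied to the same participant.** Four hypothetical cases, each observed for 20 months:

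| Case | Abstract | Primary outcomes section | Statistical analysis plan section | Sample size section |
|---|---|---|---|---|
| In local authority care for four months, still there at month 20; no offence | event | not a non-offender | no event | no event |
| Convicted of theft, stays at home | no event | event | no event | event |
| Convicted of a sexual offence, stays at home | no event | event | event | event |
| Non-sexual offence reported by the carer, no police record, stays at home | no event | event, if the supplementary report is accepted | no event | no event |

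The columns for the three named primary outcomes disagree in every row. The second row assumes that offending in the Primary outcomes section covers non-sexual offences; the section does not restrict it, and the Discussion refers to both kinds.

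**3. Sources.** Placement comes from caregivers, cross-referenced with the social care database. Offending comes from police records, with supplementation in the Primary outcomes section and without it in the sample size section. The Statistical analysis plan section names no source for sexual offences; Objective measures takes sexual and non-sexual offending from the same police records. The sources therefore differ between placement and offending, and in the supplementation, but not demonstrably between any offence and sexual offence.

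**4. Size, as illustration only.** The Background gives reconviction rates of 5–14% (sexual) and 16–54% (non-sexual). Assume that they applied at 20 months to all 80 participants:

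- sexual: 80 × 0.05 = 4 to 80 × 0.14 = 11.2, about 4 to 11 events;
- non-sexual: 80 × 0.16 = 12.8 to 80 × 0.54 = 43.2, about 13 to 43 events.

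No follow-up period is stated for these rates, non-sexual reconviction is not itself one of the candidates, and the article gives no placement rate.

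**5. Does the effect size carry over?** Take the sexual reconviction rates as the rate p under management as usual, with equal arms and no events on MST-PSB. The largest phi is then √[(p/2) / (1 − p/2)]. For p = 0.05 this is √(0.025/0.975) = 0.16; for p = 0.14 it is √(0.07/0.93) = 0.27. Both lie below 0.32. On these rates, the effect size used for conviction status could not be reached for sexual offences when MST-PSB has the lower rate.

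**The case against.** The strongest reply is that this is a feasibility trial. The primary analysis consists of Kaplan-Meier graphs and proportions per arm, with no test and no alpha. The registry entry or a separate analysis plan, neither of which is at hand, may already fix one outcome. The methods sections all centre on offending, so the Abstract could be read as a summary that went astray.

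Part of this stands. A reader might infer that three candidate outcomes inflate the false-positive risk to 1 − 0.95³ = 14.3%. The article does not support that. It plans no tests, and the candidates are not independent: sexual offences are a subset of offences, and the Primary outcomes section ties placement to offending status. A reader might also infer that the outcome will be picked once results are known. The text leaves that possible but does not show it. The sample size section should not be counted as a fourth named primary outcome either, since it only defines non-offender status.

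A reader might further conclude that the document's own weight settles the matter for placement. It does not. Placement leads in the Abstract and Discussion, offending in the methods sections, and the Discussion gives weight to both. Placement is also not free of family report, because caregivers supply it.

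What does not stand is that this is condensation or detail left to another document. These are positive statements that exclude one another. A separate plan that settled the point would still contradict part of this article.

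**Conclusion.** The contradiction is established by the text alone and needs no assumption. Three primary outcomes are named, the sample size uses a further definition, and the Primary outcomes section adds a composite rule that the Statistical analysis plan section does not follow.

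The consequence is an undetermined headline comparison and an undetermined event rate for the full trial, not a calculable error rate. The counts of about 4 to 11 against 13 to 43 in 80 show that the choice of event could matter several-fold, but only if the Background's reconviction rates hold at 20 months, which the article does not say. Nothing can be computed for placement.

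This must be corrected. The primary outcome is the plan's central commitment, and Trial status puts the trial in its third year with recruitment continuing, so outcomes may already be accruing.

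**What to change.** By a dated amendment made before anyone sees outcomes by arm, the sponsor should choose one primary outcome. It should be stated identically in the Abstract, Sample size and power calculation, Primary outcomes, the Statistical analysis plan section and the Discussion. The definition should settle:

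- the event: any offence or sexual offence, and whether a record, an arrest or a conviction is required; or placement;
- the minimum length of placement, and how participants already in short-term placement at entry, whom the inclusion criteria admit, are counted;
- whether the outcome is a composite of offending and placement;
- the data source.

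The other versions become named secondary outcomes. If offending is chosen, use official records for the main analysis and add family reports as a sensitivity analysis. If placement is chosen, rely on the social care database, with caregiver report as support. Restate the sample size for the chosen endpoint, or say plainly that the figure of 56 does not apply to it.

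The cost is wording and one amendment. No new data are needed.

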**Discussion:**

The STEPS-B feasibility trial aims to inform policymakers, commissioners of services and professionals about the potential for implementing MST-PSB as an intervention for adolescents showing problem sexual behaviour. Should MST-PSB show potential, STEPS-B will determine what would be necessary to implement the programme more fully and at a scale that would warrant a full trial.

**Trial registration:**

ISRCTN28441235 (registered 25 January 2012).

## Background

Systematic reviews of the prevalence of sexual abuse in young people indicate that 18 to 20 % of females and 6 to 8 % of males in the general population report having been abused before the age of 18 [1, 2]. Adolescents are the perpetrators of approximately 20 % of all sexual offences, and victim reports suggest that the proportion of juvenile offenders (versus adult offenders) increases as the age of the victim decreases [3]. Victims of sexual assault are at a high risk for negative sequelae [4, 5], and sexual offenders themselves engender significant social and fiscal costs, including removal from their family homes and impaired social, academic and vocational competencies as a result of their sexual offending.

Sexual offenders are heterogeneous [6, 7] and include a substantive subgroup who show many of the same risk factors as juveniles who engage in serious antisocial behaviour that does not include sexual offending [8]. For example, several studies have shown that sexual offenders share many of the same family and peer risk factors seen in non-sexual offending youth such as poor parent supervision, lower parental involvement and poorer parent-adolescent relationships, lower bonding to family and school, and higher involvement with delinquent peers [8, 9]. At the same time, a recent meta-analysis concluded that adolescent sexual offenders, when compared with adolescent non-sexual offenders, show greater atypical sexual interests (for example, sexual arousal to children or to coercive sex) and histories of child sexual abuse, higher levels of anxiety and lower self-esteem, and greater social isolation [10]. Correspondingly, while the sexual reconviction rates for adolescent sex offenders range from 5 to 14 % and are substantially lower than their reconviction rates for non-sexual offences (16 to 54 %) [11–13], reoffending rates for sexual offending are often associated with sex-specific factors [13–16], while non-sexual recidivism is related to factors commonly predictive of general delinquency [13, 15].

Despite the evolving knowledge concerning juvenile sex offenders, much less progress has been made in developing effective interventions. In a recent systematic review of interventions designed to prevent reoffending among known sex offenders and individuals at risk of sexually abusing children, Langstrom and colleagues [17] were able to identify only eight intervention studies that fulfilled their criteria, including five prospective observational studies and three randomized controlled trials (RCTs); none of these studies had been conducted in the United Kingdom. The authors concluded that an implementation of multisystemic therapy (MST) tailored towards problematic sexual behaviours (MST-PSB) [18] showed limited evidence for helping to reduce sexual reoffending in adolescent sexual offenders. However, in a meta-analysis of adolescent and adult treatment programmes of sexual offenders, Hanson and colleagues [19] pointed to the benefits of MST-PSB for reducing adolescent problem sexual behaviour and highlighted MST as a rare example of an intervention that is consistent with the risk, need and responsivity principles for effective offender rehabilitation [20]. Importantly, one of the lessons learned from the adult treatment of sexual offenders is that adult sexual offenders who attend and cooperate with treatment programmes are less likely to reoffend than those who reject the interventions [21].

### Multisystemic therapy as an intervention for problem sexual behaviours

MST is an intervention that has been developed in the United States. It has an established track record for successfully treating young people who show serious and persistent antisocial behaviour [22]. More recently, MST has been transported to other countries with some promising (Norway [23–25]) and mixed (Sweden [26] and Canada [27]) results. In the United Kingdom, following an earlier single-site trial of MST [25], a large multi-site trial is now underway, which is comparing MST with the usual services delivered to this population of young people (the START trial) [28].

Multisystemic Therapy for Youth with Problem Sexual Behaviours (MST-PSB) is an adaptation of MST aimed at adolescents who have committed sexual offences and demonstrated other problem behaviours. It is an intensive family- and home-based intervention uniquely developed to address the multiple determinants of problematic sexual behaviour in adolescents. MST-PSB is designed to reduce problematic sexual behaviours, antisocial behaviours and out-of-home placements. Problematic sexual behaviour in adolescents is sexual behaviour that is developmentally inappropriate or potentially harmful to the self or others and includes behaviour of a sexual nature that infringes on the rights of others (such as the use of coercion or force) [29].

Recent reviews of the sexual offending outcome literature [17, 30, 31] have noted that two RCTs of MST-PSB are the only published and peer-reviewed RCTs to evaluate the effects of the intervention on juvenile sexual offending, and that they have produced promising findings [18, 32]. A small efficacy trial conducted by the developers of MST-PSB reported that juvenile sex offenders receiving MST were significantly less likely than those receiving usual services to be rearrested for either sexual offences (8 % versus 46 %) or nonsexual offences (29 % versus 58 %) at 8.9 years post-treatment, and to have spent 80 % fewer days in confinement facilities [18]. A larger effectiveness trial studying the impact of MST-PSB compared with usual services through a 12-month follow-up period reported that adolescents receiving MST-PSB engaged in less problem sexual behaviour and were less likely to be placed out of the home [32].

MST-PSB is therefore the only evidence-based intervention currently available for adolescents showing problem sexual behaviour. However, despite some initial positive findings, there are several unresolved issues relating to transporting MST-PSB to other health and social care systems and jurisdictions outside the United States. First, the effectiveness of MST-PSB needs to be carefully assessed in the UK mental health, juvenile justice and social care systems. The pattern of results found in the transportability of RCT evaluations of standard MST in Canada and Europe suggest that the effectiveness of MST-PSB needs to be demonstrated by independent investigators and outside the United States. Specifically, the magnitude of the associations between standard MST and treatment outcomes are substantially higher in trials that involved the developers of the intervention (effect size = 0.81) than in studies conducted without their close involvement (effect size = 0.27) [33], suggesting a possible ‘developer effect’ (for example, therapists supervised by developers adhere more to the MST guidelines or are more motivated and engaged). Thus, an independent transportability trial is necessary to demonstrate that MST-PSB can be delivered with fidelity by UK-trained therapists. This is crucial, given that the MST-PSB adaptation requires additional skills and practices that are not part of standard MST, such as addressing parents’ and adolescents’ denial of problematic sexual behaviour. Furthermore, the intervention is being applied by MST therapists to a highly stigmatized population against which there are very strong cultural biases and prejudices. The clinical competency of UK psychologists and social workers to deliver MST-PSB with fidelity, relative to their counterparts in the United States, may also be influenced by curriculum and training differences. In addition, the relative success of standard MST may be due to the relative quality of the usual services for managing antisocial behaviour in the United States compared with usual services in other countries. MST may produce better outcomes only when usual services produce weak, null or even negative effects. Thus, the superiority and cost-effectiveness of MST-PSB needs to be demonstrated outside the United States, in studies where the therapists delivering MST are independent of the MST-PSB developers, where the comparison services or ‘management as usual’ (MAU) is consistent with the options currently available for young people showing problem sexual behaviour in that region, and where the sentencing policy within the justice system does not result in comparison with alternatives such as custodial sentences. Moreover, as noted by Littell [34] following a detailed Cochrane review of the effectiveness of MST [35], it is crucial that the research evaluation team and the developers who deliver the clinical service be completely independent.
